### Intervention

#### Control arm: SDPC for patients with T2DM

Participants in the control group will receive standard health care from community doctors, including medical counselling, regular follow-up, assessment, health education, referral advice and medical examination. 

#### Intervention arm: SDPC plus AI-HEALS-based T2DM online health education program

Participants will receive SDPC plus AI-HEALS-based intervention through the WeChat service platform "PKU Diabetes Butler" on their mobile phones, which consists of four components:1. KBQA for T2DM knowledge. Participants will be encouraged to interact with a FAQRobot (Frequently Asked Questions Robot) to accurately and efficiently gain detailed knowledge about T2DM diet (recommended or not recommended foods, food nutrients, calories, glycemic index, and glycemic load), exercise (recommended or not recommended exercise, the metabolic equivalent of physical activities), and medication management (types of medicines and how to take them), removing time and distance limitations to health care consultations and increasing health care accessibility. In addition, the FAQRobot has an entertainment function, which can tell jokes and play games with patients to calm them down. After reviewing guidelines, professional literature, and consulting experts, we identified the source material and knowledge for the T2DM self-management KQBA. Subsequently, we uploaded the underlying data to the Bot Factory^22^ Dialogue AI Platform produced by Emotibot [67], which formed an automated Q&A bot with semantic understanding and automatic knowledge mining. The Q&A bot was linked to the WeChat platform "PKU Diabetes Butler". The backend stores the questions that participants asked as well as their usage behaviors (such as time and frequency) so that we can improve the knowledge graph regularly and assess the usage patterns of participants.2. Recording and monitoring of physiological indicators as well as lifestyle behaviors. Participants will be encouraged to record information on physiological indicators (blood glucose, blood pressure), diet, physical activity, and medication-taking regularly on the platform, which stores and uploads the records electronically and enables long-term monitoring of blood glucose control and changes in self-management behaviors.3. A reminder service for taking medications and monitoring blood glucose levels. Participants will be encouraged to enter the time they want to be reminded in the system, and the platform can remind them to take their medication or monitor blood glucose levels at specified time.4. Automated and personalized messaging about diabetes self-management. Participants will receive 1–3 automated messages about T2DM control and management per week, the content of which will be based on multi-theory model (MTM) of health behavior change, and will contain knowledge of T2DM diet, exercise, and medication taking to increase health literacy and to encourage behavioral change. Furthermore, based on the questions users ask the FAQRobot, the system will accurately push additional, tailored articles. Researchers will also regularly log into the backend to check the number, type and time of articles read by the participants in order to tailor the content and frequency of messages to their reading patterns.

All user data will be kept confidential. Participants have the option to withdraw from the study at any time. Adverse events related to the intervention will be recorded and reported in accordance with local procedures.

### Outcomes

Primary outcome: Change of HbA1c from baseline to 1, 3, 6, 12, and 18-month follow-up.

Secondary outcomes:1. Modifications of self-management behaviors: dietary, physical activity, blood glucose monitoring, and medication adherence.2. Social cognition and psychology: diabetes health literacy, self-efficacy, depression, anxiety and stress.3. Metabolic control: self-reported fasting plasma glucose or 2 h plasma glucose, dose of insulin and medicine, other indicators such as blood pressure, blood lipids, and BMI.4. Economic evaluation: A comparison of incremental cost-effectiveness ratios (ICERs) will be conducted between the AI-HEALS-based intervention and usual care of T2DM. Therefore, health-related quality of life (HRQoL), healthcare utilization, including medical consultations, use of healthcare (outpatient, hospitalized, and primary care services), medicine purchases, accident visits, and direct non-medical costs (diabetes-related transportation, lodging) will be collected.

Additionally, the rate of recruitment and drop-out, as well as the reasons for drop-out, will be gathered. To determine whether the data is homogeneous, demographic characteristics and study outcomes will be compared between people dropping out and participants resistant to the entire trial during data analysis.

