**Methods:**

This is a nested mixed-method study that includes a community-based cluster-randomized control trial and personal in-depth interviews. Individuals with T2DM between the ages of 18 and 75 will be recruited from 40-45 community health centers in Beijing, China. Participants will either receive standard diabetes primary care (SDPC) (control, 3 months) or SDPC plus AI-HEALS online health education program (intervention, 3 months). The AI-HEALS runs in the WeChat service platform, which includes a KBQA, a system of physiological indicators and lifestyle recording and monitoring, medication and blood glucose monitoring reminders, and automated, personalized message sending. Data on sociodemography, medical examination, blood glucose, and self-management behavior will be collected at baseline, as well as 1,3,6,12, and 18 months later. The primary outcome is to reduce HbA1c levels. Secondary outcomes include changes in self-management behavior, social cognition, psychology, T2DM skills, and health literacy. Furthermore, the cost-effectiveness of the AI-HEALS-based intervention will be evaluated.

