## Methods

### Study design

This study will use a nested mixed-method study with a quantitative survey and a qualitative interview to gain a better understanding of the effect and acceptability of the AI and mHealth-based intervention program for T2DM. The research will take place from August 2023 to June 2025. The quantitative survey will be conducted as a community-based cluster randomized controlled trial with two parallel groups to compare the effectiveness of the AI-HEALS-based education program on T2DM control and self-management behaviors (such as medication use, dietary and physical activity modification). The intervention will last three months. Questionnaires, physical examinations, and personal in-depth interviews (the qualitative study) will be conducted to participants at baseline, 1, 3, 6, 12, and 18 months to examine changes in self-management behaviors and blood glucose control. Cost-effectiveness analysis will be conducted at 12 and 18 months. The flow chart for the study shown in Figs. 1 and 2.

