### Effect size

Based on our previous study, assuming an alpha risk of 0.05, a beta risk of 0.10, an intraclass correlation (ICC) of 0.002, a mean level of HbA1c in patients with type 2 diabetes of 7.13%, and a standard deviation (SD) of 1.60%, at least 2 clusters, and 166 subjects (138 total before considering a dropout rate of 20%) in each cluster are expected to be recruited according to the sample size formula for unmatched studies [66] to detect a decrease in HbA1c to 6.50% after the intervention. As a result, a total of 664 patients in 4 communities are required to be recruited for this program.

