### Statistical analysis

Data from the quantitative study will be recorded in the designed questionnaire and double-parallelly entered into Epidata 3.1 (Version 15.0.5, Odense, Denmark). Variables analysis will be based on the premise of intention to treat. Continuous variables will be presented as mean ± SD (M(P_25_, P_75_), if they are abnormal distribution), and be compared using Student's t test or one-way ANOVA (or non-parametric tests if necessary). Data distribution will be identified by a Kolmogorov–Smirnov test. Categorical data reported as n(percentage of sample) will be compared using χ2 tests. With regard to the cross-sectional analysis, linear regression, logistic regression and structural equation model (SEM) will be conducted to explore the influence factors of behaviors pattern and mHealth usage pattern evaluated by the group-based trajectory model (GBTM). For longitudinal data, a generalized linear mixed model (GLMM) will be used to identify the effectiveness of the AI and mHealth-based intervention in behavioral changes and diabetic control. Set an alpha risk of 0.05 for two-sided tests. Data will be analysed using IBM SPSS Statistics version 24.0 (SPSS Inc., an IBM Company, Chicago, Illinois, USA), Stata (version 14.0, Stata Corporation, College Station, TX) and M*plus* (version 7.4, Muthén & Muthén, Los Angeles, CA, USA).

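### The primary outcome gives five HbA1c visits equal status, one of them (1 month) not scheduled in Table 1, and the article does not say which visit or contrast decides success

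*Protocol article*

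**What the plan says.** - **Outcome.** The Outcomes section gives the primary outcome as "Change of HbA1c from baseline to 1, 3, 6, 12, and 18-month follow-up". No visit is ranked above another. The Abstract says only that "The primary outcome is to reduce HbA1c levels", with no time point.
- **Schedule.** In Table 1 (Variables measurement) the HbA1c row is ticked at 0, 3, 6, 12 and 18 months, and the 1-month cell is empty. The anthropometric and questionnaire rows are ticked at 1 month.
- **General wording on timing.** The Abstract lists blood glucose among the data that "will be collected at baseline, as well as 1,3,6,12, and 18 months later". Study design and Variables measurement place physical examinations at the same visits, and Study design links them to blood glucose control.
- **Sample size.** The Effect size section works "assuming an alpha risk of 0.05, a beta risk of 0.10, an intraclass correlation (ICC) of 0.002", with "a mean level of HbA1c in patients with type 2 diabetes of 7.13"%, an SD of 1.60% and a post-intervention target of 6.50%. No month is attached to that target.
- **Duration.** Study design states "The intervention will last three months".
- **Analysis.** Statistical analysis names a generalized linear mixed model for longitudinal data and adds "Set an alpha risk of 0.05 for two-sided tests". It does not say which contrast answers the primary question.

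**The concern.** There are two faults in how the primary outcome is fixed.

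First, the outcome definition and the measurement schedule disagree about 1 month. An analysis plan cannot settle this, because it concerns whether blood is drawn.

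Second, the visits ask different questions. At 3 months the contrast measures the effect at the end of a three-month programme. At 6, 12 and 18 months it measures whether the effect persists after the programme has stopped. The sample size covers one comparison, but the definition gives equal standing to several. Without a named visit or joint test, a claim of glycaemic benefit could rest on whichever visit turns out significant. A benefit at 3 months that fades, or one seen only at 12 months, could be reported as a positive or a negative trial with equal textual support.

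**Working it through.** **1. Setting the passages side by side on 1 month**

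| Place | HbA1c at 1 month? |
|---|---|
| Outcomes | Yes, part of the primary outcome |
| Table 1, HbA1c row | No tick |
| Abstract, Methods | Blood glucose data listed for 1 month, HbA1c not named |
| Study design; Variables measurement | Physical examinations at 1 month, HbA1c not named |

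Table 1 is the only place shown that schedules HbA1c row by row. By that table, four of the five primary components (3, 6, 12 and 18 months) can be computed.

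**2. What the sample size was built for**

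Inputs from the Effect size section: difference d = 7.13 − 6.50 = 0.63, SD = 1.60, alpha 0.05, power 90%.

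Two-means formula, two-sided: n = 2·SD²·(1.960 + 1.2816)² / d² = 2 × 2.56 × 10.507 / 0.3969 = 135.5, so 136.

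The unmatched-cluster formula, solved with two clusters per arm and 0.002 entered as the between-cluster coefficient of variation, gives m = 5.12 / (0.3969/10.507 − 0.002² × (7.13² + 6.50²)) = 136.9, so 137.

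The article states 138, and both results are within 2% of it. A one-sided test would give 111, which does not fit. The remaining steps follow: 138 × 1.2 = 165.6, so 166, and 4 × 166 = 664. The stated figure is therefore consistent with one comparison at two-sided 0.05, with nothing set aside for several visits.

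**3. Error rate if any scheduled visit could count as success**

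This rule is an assumption, as the article does not state it. For four independent tests at two-sided 0.05:

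- any false positive: 1 − 0.95⁴ = 18.5%
- a false positive favouring the intervention: 1 − 0.975⁴ = 9.6%, against 2.5% for a single test

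The visits share patients and a baseline value, so the test statistics will be correlated. The article gives no correlation. For four equally correlated normal statistics:

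| Assumed correlation | Any false positive | Favouring the intervention |
|---|---|---|
| 0 | 18.5% | 9.6% |
| 0.5 | 15.6% | 7.8% |
| 0.7 | 13.0% | 6.5% |
| 0.8 | 11.4% | 5.7% |
| 0.9 | 9.4% | 4.7% |
| Single named visit or one joint test | 5% | 2.5% (named visit) |

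**4. Price of keeping four separate primary visits**

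With Bonferroni, alpha per visit is 0.05/4 = 0.0125. The formula in step 2 then gives 5.12 × (2.498 + 1.2816)² / 0.3969 = 184.2, so 185 in place of 136. That is 185/136 = 1.36, or 36% more before dropout. With one named visit, the single-test basis of the stated number is unchanged.

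**The case against.** **The article does not plan four tests.** A reader might infer that each visit is tested at 0.05 and that any one success suffices. The text does not say this. It names one mixed model and one alpha, and a group or group-by-time test from that model would be a single test at 0.05 with no inflation. This objection stands, so the error rates above are conditional.

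**The contrast may be in an analysis plan that is not shown.** Model detail and multiplicity handling are commonly left there, and their absence is not the fault raised here. But the article does define the primary outcome, and it does so with five equal visits, one of which its own schedule omits. Which visit is primary belongs with that definition, and the sample size depends on it.

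**HbA1c might be measured at 1 month after all.** A reader might conclude from Table 1 that it never is. That rests on Table 1 alone. The Abstract and Study design point loosely the other way, and the assessment schedule in Fig. 2 was not available to this review. Nor is the HbA1c row the only follow-up row without a 1-month tick: the economic evaluation is ticked only at 12 and 18 months. The supportable statement is that the passages conflict.

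**Three months is already implied.** A three-month intervention and a sample size for the post-intervention value do point that way. That supports naming 3 months, but the Outcomes section still does not do so.

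**The largest figure overstates the risk.** Independence is implausible for repeated measures on the same patients, and half of the false positives would favour control or nearly so. The range with correlation, and the column favouring the intervention, are the fairer guides.

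**Conclusion.** The point holds in this form: the primary outcome is badly fixed. It includes a 1-month HbA1c change that Table 1 does not schedule, and it gives all visits equal status although the trial was sized for one comparison.

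The 1-month conflict and the lack of a named visit can be read directly from the text. The error inflation depends on two assumptions: that any one of the four scheduled visits could count as success, and the between-visit correlation. Under both, the two-sided false-positive chance is 9.4% to 15.6% for correlations of 0.9 to 0.5, with 18.5% as the independent limit. In favour of the intervention it is 4.7% to 7.8%, with a limit of 9.6%, against 2.5%. Under a single joint test or one named visit there is no inflation. The documents do not support saying that the trial will run at these error rates. They leave open a choice that could lead there.

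**What to change.** **Preferred.** Before recruitment, name one primary endpoint in Outcomes: the difference between arms in HbA1c change from baseline to 3 months, estimated from the mixed model and tested at two-sided 0.05. This matches the length of the intervention, the post-intervention comparison in the sample size, and a visit at which Table 1 schedules HbA1c. List 6, 12 and 18 months as secondary, as evidence on persistence.

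**If the investigators prefer to keep all visits primary.** State either one joint test of the arm difference across the scheduled visits or a Holm adjustment, and check the sample size against that choice.

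**In either case.** Reconcile the 1-month entry across Outcomes, the Abstract, Study design and Table 1. Removing 1 month from the HbA1c outcome needs no extra blood draw; keeping it means adding a draw to Table 1. Check that the registry entry, which was not seen here, carries the same definition.

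**Cost.** A sentence or two of text. The article says recruitment had not begun, so the change can be made before any outcome data exist. The real cost is that the later visits lose primary status, which matters if the investigators regard lasting control as the main question.

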### Variables measurement

Sociodemographic variables will be obtained at baseline. Physical examinations and questionnaire surveys will be completed at baseline, 1, 3, 6, 12, and 18 months (Table 1).

**Table 1 Tab1:** Data collection components and collection timeline

Type of research	Data collection component		Timepoint					
			0 M	1 M	3 M	6 M	12 M	18 M
Quantitative research	Sociodemographic variables	sex, age, marital status, location, family average household, educational level, occupation, clinical information	√					
	Blood glucose	HbA1c levels	√		√	√	√	√
	Anthropometric variables	height, weight, waist circumference, and blood pressure	√	√	√	√	√	√
	Self-management behavior	Questionnaire: SDSCA	√	√	√	√	√	√
	Dietary intake	Questionnaire: self-administered diabetes eating behavior questionnaire	√	√	√	√	√	√
	PA	Questionnaire: IPAQ-SF	√	√	√	√	√	√
	Medication taking	Questionnaire: ARMS	√	√	√	√	√	√
	Emotional stage	Questionnaire: GAD-7, PHQ9, and PSS-4	√	√	√	√	√	√
	T2DM knowledge and skills	Questionnaire: HLS-SF12 and self-designed 9-item diabetes self-management skills scale	√	√	√	√	√	√
	Self-efficacy	Questionnaire: self-designed diabetes self-management scale	√	√	√	√	√	√
	Behavioral change	Questionnaire: self-designed 31-item MTM scale for health behavior change	√	√	√	√	√	√
	Quality of life	Questionnaire: EQ-5D-5L	√	√	√	√	√	√
	Economic evaluation	healthcare utilization (medical consultations, use of outpatient, hospitalized, and primary care services, medicine expenditures, accident visits, and lost productivity)					√	√
	Cloud data	KQBA interaction records and user reading behavior data		√	√	√	√	√
Qualitative research	Person-in-depth semistructured interview	User experience of the AI-HEALS		√	√	√	√	√

Sociodemographic variables: sex, age, marital status, location, family average household, educational level, and occupation will be gathered, as well as clinical information such as the duration of T2DM, detailed medical history, and current diabetes medications.

Measurement of blood glucose: HbA1c levels will be measured by drawing venous blood fasting.

Anthropometric variables: height, weight, waist circumference, and blood pressure of each participant will be measured twice by certified instruments. Height and body weight will be measured using an adequately calibrated certified electronic instrument. Divide weight (kg) by height (m) to calculate the BMI. Waist circumference will be measured at the level of the umbilicus using a tape measure. As regards blood pressure, systolic and diastolic BP will be measured by a validated automated sphygmomanometer.

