### Economic evaluation

To assess the efficacy of this mHealth education program on health equality, the economic evaluation will be reported as ICERs and compared between the AI-HEALS-based intervention and traditional T2DM primary care. During the trial, the economic cost of healthcare utilization (medical consultations, use of outpatient, hospitalized, and primary care services, medicine expenditures, accident visits, and lost productivity) will be assessed per case, as well as the cost of project implementation (AI-HEALS-based interventions (plus primary usual care activities) versus primary usual care activities). Utility will be evaluated in terms of HRQoL, with data from the EQ-5D-5L used to calculate health utility values.

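### Table 1 schedules healthcare-use and cost items only at months 12 and 18, with no baseline and nothing near the 3-month intervention, which weakens the cost side of the ICER wherever these items are self-reported

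*Protocol article*

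**What the plan says.** The Economic evaluation row of Table 1 (Variables measurement) covers "healthcare utilization (medical consultations, use of outpatient, hospitalized, and primary care services, medicine expenditures, accident visits, and lost productivity". It is blank at 0, 1, 3 and 6 months and ticked at 12 and 18 months. The Quality of life row ("Questionnaire: EQ-5D-5L") is ticked at 0, 1, 3, 6, 12 and 18 months.

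Study design states: "The intervention will last three months". It also states: "Cost-effectiveness analysis will be conducted at 12 and 18 months". The analysis times therefore match the two ticks in the cost row.

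The Economic evaluation section sets the period to be costed with the words "During the trial, the economic cost of healthcare utilization", to be assessed for each case, and adds programme delivery separately: "as well as the cost of project implementation". The Outcomes section also lists diabetes-related transport and lodging among the costs to be collected. On data source, Statistical analysis says: "Data from the quantitative study will be recorded in the designed questionnaire". The article gives no look-back period for the cost items and mentions no claims or clinic-record extraction.

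**The concern.** An ICER divides an incremental cost by an incremental effect over the same period. Here the effect side is measured six times from baseline onward. The cost side is measured twice, first at month 12. The article wants costs over the trial, but nothing on cost is scheduled before, during or soon after the three months in which the two arms are treated differently.

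If participants supply the information, the month-12 question must reach back a full year to cover the trial. Otherwise it leaves part of that year uncosted, starting with the intervention period. Small, frequent items such as consultations and medicine purchases are hard to recall over a year.

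The absence of a baseline cost matters because allocation is by cluster. Spending habits can differ between health centres by chance, and without a baseline measure that difference cannot be taken out directly.

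There is a further consequence if costs are collected at the visits. A participant who leaves between months 6 and 12 may have up to four EQ-5D-5L measurements (0, 1, 3 and 6 months) and no healthcare-use data. The sample-size section allows for 20% dropout but not for its timing, so the extent of this loss is unknown.

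Cost-effectiveness is part of the third specific objective, so the economic result is one the trial sets out to deliver.

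**Working it through.** No power or sample-size figure enters this point. The check is a reading of the schedule and simple subtraction.

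**Inputs**
- Cost collection at 12 and 18 months (Table 1, Economic evaluation row).
- EQ-5D-5L at 0, 1, 3, 6, 12 and 18 months (Table 1, Quality of life row).
- Intervention length of 3 months (Study design).
- Cost-effectiveness analysis at 12 and 18 months (Study design). This agrees with the ticks in the cost row, so the two-tick reading of the table is sound.

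**Step 1: collection points.** Cost side 2, utility side 6. Baseline cost measurements: 0.

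**Step 2: gap after the intervention.** 12 − 3 = 9 months from the end of the intervention to the first cost collection.

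**Step 3: look-back needed for full coverage by self-report.** Month 12: 12 − 0 = 12 months. Month 18: 18 − 12 = 6 months.

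**Step 4: shorter look-backs at month 12.** The article gives no window, so the values of *r* below are assumptions chosen to show the range. A look-back of *r* months covers month 12 − *r* to month 12. It leaves 12 − *r* months of the first year uncovered and includes max(0, 3 − (12 − *r*)) of the three intervention months.

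| Assumed look-back *r* (months) | First-year months uncovered | Intervention months covered |
|---|---|---|
| 1 | 11 | 0 of 3 |
| 3 | 9 | 0 of 3 |
| 6 | 6 | 0 of 3 |
| 9 | 3 | 0 of 3 |
| 12 | 0 | 3 of 3 |

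Only a window longer than 9 months reaches the intervention at all, and only a 12-month window covers it fully.

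**Step 5: the same check with collection at 0, 3, 6, 12 and 18 months.** After baseline, the look-backs are 3 − 0 = 3, 6 − 3 = 3, 12 − 6 = 6 and 18 − 12 = 6 months. The longest falls from 12 to 6 months, the intervention period is covered by one 3-month question at its end, and a baseline cost exists.

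**The case against.** The strongest reply is that the article never says these items are self-reported. In Table 1 the instrument rows are labelled as questionnaires and the Economic evaluation row is not. The descriptions of the questionnaires include none on healthcare use. The sentence on recording data in a questionnaire covers all quantitative data, including venous HbA1c, so it describes the data form rather than the source. Extracting visits, admissions and medicines from records at months 12 and 18 would fit the ticks and leave neither a recall problem nor a gap. Source and look-back window are also details that an article may leave to the full protocol.

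Much of this stands, and it makes the point conditional. It does not remove it. Lost productivity, transport and lodging are unlikely to be in clinic records, so for those items the choice between long recall and a gap remains. The point does not rest on the unstated window: under self-report, every window has one defect or the other, given the schedule that Table 1 fixes.

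Several stronger readings are tempting and are not supported:
- *The ICER necessarily rests on 12-month recall or on missing costs.* This holds only for self-reported items.
- *All intervention-period costs may be missing.* Programme delivery cost is counted separately. Only healthcare-use and related participant costs are in question.
- *A fixed share of follow-up is unobserved.* Any such share depends on a window that the article does not give.
- *Forgetting differs by arm.* Intervention participants are encouraged to log glucose, blood pressure, diet, activity and medication-taking. None of these is a consultation, an expenditure or a productivity loss, so differential recall is only a possibility.
- *The article contradicts itself.* The analysis times and the cost ticks agree. That one was copied from the other would be a guess.

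On the baseline, randomization means that the ICER can be computed without it. Related covariates are collected at baseline: diabetes duration, medical history, current medication and EQ-5D-5L. They are partial substitutes for baseline cost.

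**Conclusion.** The point holds as a weakness in the stated schedule. Cost items are first collected at month 12, 9 months after the intervention ends, with no baseline, while utilities for the same ICER are measured six times. To the extent that the items are self-reported, full coverage needs a 12-month recall, and any month-12 window of 9 months or less captures no healthcare-use cost from months 0-3. This very likely applies to lost productivity, transport and lodging, and it applies to every item if no records are used.

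Without a baseline cost, chance differences in spending between clusters cannot be adjusted for directly. How much that matters depends on the number of clusters, which the article gives as 40-45 health centres in one place and 4 communities in another.

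A reader might infer that incremental cost is biased by a known amount or in a known direction. The article gives no cost data from which either could be derived. What can be said is that incremental cost will be less precise than it need be and may be biased. The outcome is secondary and economic, and the HbA1c analysis is untouched. The change is worth making because it is cheap before recruitment, and self-reported costs that are not asked about in time are hard to recover later.

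**What to change.** In Table 1, tick the cost items also at the existing 0, 3 and 6 month visits. Ask about the period since the last cost visit and, at baseline, about a fixed prior period such as 3 months. Include the transport and lodging costs named under Outcomes. Sum the periods for the ICERs, which stay at 12 and 18 months, and adjust incremental cost for baseline cost.

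Where visits and medicines can be taken from records, state this, extract them for the whole period including a pre-baseline window, and limit the added questions to items that records do not hold.

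The cost is a few more minutes for participants at three visits that already take place, plus the extra data entry. The article says that recruitment had not begun, so on that timing no collected data would be affected.

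### The article's BMI formula omits the square on height; applied as written, every BMI value and change would be too large by a factor equal to height in metres

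*Protocol article*

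**What the plan says.** In the Anthropometric variables paragraph under Variables measurement, the article first describes the raw readings: "Height and body weight will be measured using an adequately calibrated certified electronic instrument". It then gives the derivation: "Divide weight (kg) by height (m) to calculate the BMI". No exponent and no word for squaring appears, and no other section offers a different BMI formula.

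The Outcomes section places BMI in the third group of secondary outcomes, metabolic control, which closes with "other indicators such as blood pressure, blood lipids, and BMI". Table 1 schedules height and weight at all six visits (baseline and months 1, 3, 6, 12 and 18), so BMI can be derived up to six times per participant.

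**The concern.** BMI is weight in kilograms divided by the square of height in metres. The article's rule divides by height once. The sentence is an instruction for computing a variable that the same article lists as an outcome, so it is more than loose background wording. Nor is this a detail left for a fuller document: the article chose to state the formula and stated it wrongly.

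Three things are at stake if an analyst codes the rule literally:

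- The values would have the wrong size and the wrong unit (kg/m), so they could not be set beside BMI figures in kg/m².
- Changes from baseline would be overstated by the same factor as the levels.
- The factor differs from person to person, so two people with the same true BMI would receive different values, and no single constant would correct a reported mean.

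**Working it through.** **Inputs.** The stated rule is weight/height (Variables measurement). The standard definition is weight/height². The article reports no BMI value, so there is no figure of its own to reproduce. It also gives no heights or weights, so the body sizes below are assumptions for illustration.

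**Ratio of stated to correct value.** With weight w in kg and height h in m:

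(w/h) ÷ (w/h²) = h

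The error factor is therefore the person's height in metres and does not depend on weight. Only a height of exactly 1 m would give the right number.

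**Levels.**

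| Assumed weight, height | Stated rule, w/h | Correct, w/h² | Factor |
|---|---|---|---|
| 55 kg, 1.55 m | 55/1.55 = 35.5 | 55/2.4025 = 22.9 | 1.55 |
| 70 kg, 1.70 m | 70/1.70 = 41.2 | 70/2.89 = 24.2 | 1.70 |
| 80 kg, 1.75 m | 80/1.75 = 45.7 | 80/3.0625 = 26.1 | 1.75 |

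Over assumed heights of 1.55 to 1.75 m the excess is 55 to 75%. Over a wider assumed range of 1.45 to 1.90 m it is 45 to 90%.

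**Changes.** For a 2 kg loss at an assumed 1.60 m, the stated rule gives −2/1.60 = −1.25. The correct change is −2/1.60² = −0.78 kg/m². The ratio is again 1.60.

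**What is preserved.** For an adult whose height stays constant, the sign of the change is unaffected. So is the percentage change, because height cancels: (−2/h) ÷ (w/h) = −2/w, the same as under the correct formula.

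**Comparison between people.** Take two people who share the correct BMI of 24.22 (the 70 kg, 1.70 m value) but are 1.55 m and 1.75 m tall. The stated rule gives 24.22 × 1.55 = 37.5 and 24.22 × 1.75 = 42.4. The gap of 24.22 × 0.20 = 4.8 comes from height alone.

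**The case against.** The strongest reply is that this is probably a slip of wording in a condensed article, and that whoever computes BMI will use the usual formula. That may well be so. It makes the consequence conditional on the sentence being followed, but it does not make the sentence right, and nothing else in the article corrects it.

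A second reply is that an exponent may have been lost when the text was read from the PDF. This is unlikely. A superscript survives elsewhere in the same text ("Bot Factory^22^ Dialogue AI Platform"), and the wording here shows no trace of one. The printed page itself was not available to settle it.

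A third reply concerns reach, and it stands. BMI comes last in an open list within one of four groups of secondary outcomes. The primary outcome is HbA1c, the sample size is built on HbA1c, and the Population section has no BMI criterion. Raw height and weight are recorded, so no information is lost.

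A reader might also infer larger harms, which the article does not support:

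- *Confounding of the treatment comparison by height.* With stable adult height, the rule multiplies each person's BMI and BMI change by a constant of their own. In a randomised comparison this changes the unit and gives taller people more weight, but it does not by itself confound the comparison.
- *Corrupted adjusted models or BMI categories.* The article names no model adjusted for BMI and uses no BMI cut-off.
- *Nearly all participants appearing severely obese.* The article gives no distribution of body size and no obesity threshold from which this could be derived.

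**Conclusion.** The formula is wrong as written and should be corrected. If it is followed literally, each BMI value and each BMI change is too large by a factor equal to the participant's height in metres, the unit is kg/m, and comparisons between people of different height are distorted. The factor itself is exact algebra; the range of 55 to 75% and the worked examples rest on assumed heights and weights.

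It would go too far to say that every BMI the trial reports will be wrong: that follows only if the sentence is coded as it stands, and the article cannot show whether it will be. This is a plain error in the definition of one secondary indicator. It is recoverable from the raw data and poses no threat to the primary analysis.

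**What to change.** Replace the sentence under Variables measurement with: BMI = weight (kg) / [height (m)]², in kg/m². Check that any derivation code uses the same formula.

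The cost is one line of text, with no change to data collection, visits or sample size. The Population section says recruitment had not begun when the article was written, so at that point the correction could precede any data. If BMI has since been computed by the stated rule, it can be recalculated from the recorded heights and weights.

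The article says that the measurements are taken twice but not how the two readings are combined. That detail may sit in a fuller document, and the correction does not depend on it.
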